## Abstract

**Background::**

Head and neck tissue defects cause great physical and psychological damage to patients. Therefore, accurate positioning of perforating vessels before operation is of great significance for improving the success rate of flap preparation and avoiding unnecessary incision injury.

**Methods/Design::**

A total of 60 patients with laryngeal cancer in otolaryngology, Department of Otolaryngology Head and Neck Surgery, Affiliated Hospital of Southwest Medical University and the Third People's Hospital of Mianyang city from October 2020 to October 2021 will be selected and randomly divided into CT angiogram (CTA) group (n=20), mimics group (n = 20) and CTA + mimics group (n = 20) according to the numerical table. Patients in the CTA group will receive CTA examination of lower extremities. Patients in mimics group will receive digital technology in the positioning of perforator. Patients in CTA + mimics group will receive CTA + digital technology. All the patients will receive the flap cutting and the flap making; the doctor will determine the perforation branch of the flap with 3-D visual positioning, measure the preoperative indicators intraoperatively and complete the wound repair. Finally, the survival rate, sensitivity, specificity and accuracy of the flap will be measured.

**Discussion::**

The anterolateral thigh flap has been widely used to repair various tissue defects and has obtained good clinical results. The extensive clinical application mainly focuses on 2 aspects, namely the study of vascular anatomy of lateral flap and the exploration of preoperative flap design technology. Perforator is the direct blood supply source of anterolateral thigh flap, so it is particularly important to study the anatomy of perforator. Therefore, this study will reveal CTA combined with digital technology in the vascular anatomy of the anterior external femoral flap and the design of the flap before and during surgery, so as to provide help for the repair of tissue defects.

**Trial registration::**

It has been registered at http://www.chictr.org.cn/listbycreater.aspx (Identifier: ChiCTR2000038951), Registered on October 10th, 2020.

## Introduction

1

Head and neck tissue defects are often caused by trauma or infection caused by tumor resection.^[1]^ Tissue defects in the head, neck, maxillofacial and oral cavity lead to facial damage, and affect the patient's breathing, chewing, swallowing, speech and other physiological functions, thus affecting the patients quality of life.^[2]^ Therefore, the reconstruction of head, neck and maxillofacial tissue defects and the ideal reconstruction of morphology and function are urgent problems for surgeons. At present, the proximal pedicle flap repair is a common way to repair head and neck soft tissue defect. However, for patients with large defects and near tumor metastasis, the operation of adjacent pedicled tissue flap is limited.^[3]^ With the rapid development of microsurgical techniques, vascular anastomosis free tissue flap repair has been widely used, and the success rate of vascular anastomosis has gradually increased.^[3,4]^ The anterolateral thigh flap (ALTF) has been most widely used for reconstruction of head and neck defects.^[5]^

Interactive control system software-Materialises interactive medical image control system (MIMICS) has been broadly applied in medical researchers,^[6,7]^ some scholars tried to apply 3-D to perforator localization and the design of the flap, flap perforators through the analysis of the 3-D visualization of blood vessels of the origin, contorts, within the muscle skin distribution relationships, and rebuild the precise 3-D visualization flap model.^[8]^ CT angiogram (CTA) technology combined with 3-D software has gradually been used to study vascular anatomy of flaps and preoperative flap design, its feasibility and some advantages have been reported.^[9]^ However, such studies are not yet mature, and there are few clinical studies on the preparation of anterolateral thigh flaps, so the feasibility remains to be further explored and improved.

## Methods/design

2

### Research object

2.1

We aim to compare the efficacy including survival rate, sensitivity, specificity and accuracy of in patients divided into CTA group, mimics group and CTA + mimics group in the repair of head and neck soft tissue defects with anterolateral thigh flap.

### Study method

2.2

1.The patients will complete routine preoperative examination to exclude serious systemic diseases, and received enhanced valvular CT scan, so that the doctor could determine the lesion scope and vascular condition in the recipient area;2.The patients will be placed in the supine position, the middle and upper 1/3 of both lower extremities will be radiographically marked, and both lower extremities will be kept naturally straight. Iohexol injection will be injected intravenously from the middle of the elbow. A 256-slice spiral CT (Philips, USA) will be used for continuous CTA scanning from bilateral anterior superior iliac spine to bilateral lower edge of patella. CT scanning parameters will be set as 0.625 mm thickness, 120-140 kV, and 525 mA.3.CTA data preprocessing, search for puncture and define reconstruction area: obtain CTA data in DICOM format and import CTA data into 3-D15.0 software (Materialize, Belgium). After reading the data, 3-D15.0 software automatically creates a 3-D project file and uses the convert function to complete the data conversion and generate the original CTA image. Based on the original cross section, the software automatically reconstructs the continuous sectional images of sagittal plane and coronal plane to form the observation screen of 3 dimensions. The original CTA images will be scanned and observed in three orthogonal sectional views to determine the appropriate location of the perforation of the anterolateral femoral flap. Then, the 3-D reconstruction area will be restricted to 1 side of the supply area with suitable cutting struts with Crop Mask, thus reducing the workload of data segmentation in later period.4.3-D is used to reconstruct bones, blood vessels and skin: a section line is created by using the section line option in the axial window, and the gray value distribution along the line can be obtained. To better observe the transition of soft tissue, cortical bone and cancellous bone, click the option of Start Thresholding and select a certain amount of pixel gray value to segment the bone from anterior superior iliac spine to ipilateral patella. The soft tissue and some discrete voxels are then separated from the bone by means of regional growth. Select the region growth tool from the segmentation toolbar and click on the bone section to add all associated voxels to the new mask. The hip, femur, and patella will be extracted from the shape and outline of the bone at each axis view level using a multi-layer editing tool. The newly added mask will be reconstructed in 3-D to extract the individual bone model. Adjust appropriate thresholds to create a new mask, use a multi-layer editing tool on the axis view to erase irrelevant grayscale values, and retain and extract major blood vessels and perforations. The erased new mask will be reconstructed in 3-D, and the reconstructed plane mask will be duplicated. Use the Edit Mask in 3-D to edit the reconstructed 3-D model. Remove the irrelevant soft tissue with the cover lock tool. Click the erase tool to remove the selected pixels from the Mask. After the 3-D editing function is completed, close the toolbar and carry out 3-D reconstruction on the edited corresponding plane mask, so as to obtain clear blood vessels and perforating branches. Reconstruct the thigh skin, create a new mask, set the segmentation threshold, erase the gray value of irrelevant structure on the axis view, carry out 3-D reconstruction, and use the wrap function to make the reconstructed skin continuously smooth.5.3-D visualization of the model: give bone and blood vessel an opaque and skin transparency High, which allows observation and determination of bone and blood vessel through the skin. To enhance the visual effect, the target perforations and pedicles can be stained to a specific color. Based on the size and shape of the wound in the receiving area and the cutting function in the simulation option, the scope, depth and path of the flap will be simulated along the skin surface to generate a 3-D visual model of the personalized free anterolateral thigh flap.6.Simulated skin flap removal and operation: 3-D will be used to edit and process the reconstructed 3-D model before surgery. After other parts will be hidden, the designed anterolateral thigh flap will be “removed” from the 3-D model together with the vascular pedicle. The simulated data will be transferred to the intraoperative body surface of the patients, and the flap will be surgically removed to verify the accuracy of perforator location, and the anterolateral thigh flap will be transplanted and repaired for head and neck soft tissue defects.7.Routine nursing care after free flap transplantation will be given to promote wound healing. Preoperative and intraoperative measurement data will be processed and analyzed with SPSS20.0 software.

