### Interventions

2.4

Patients will be randomly divided into CTA group (n = 20), mimics group (n = 20) and CTA + mimics group (n = 20) according to the numerical table. Patients in the CTA group will receive CTA examination of lower extremities. Patients in mimics group will receive digital technology in the positioning of perforator. Patients in CTA + mimics group will receive CTA + digital technology. All the patients will receive the flap cutting and the flap making; the doctor will determine the perforation branch of the flap with 3-D visual positioning, measure the preoperative indicators intraoperatively and complete the wound repair. Finally, the survival rate, sensitivity, specificity and accuracy of the flap will be measured.

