### Measurement of outcomes

2.5

Vascular anatomy and preoperative design results of the anterolateral thigh flap will be recorded, and intraoperative and preoperative comparisons will be analyzed to explore the clinical efficacy of postoperative patients. After the completion of image digitization, 2 physicians who have been working on the anterolateral thigh flap for more than 4 years read the images in a double-blind way to evaluate whether the location, shape, and scope of the lesion of the patient has invasion or metastasis. When opinions will be different, they read the images together and agreed. Consistency analysis by CTA joint digital technology, digital technology and CTA in the defects of head and neck cancer patients in the orientation of value, when the CTA inspection found perforators preoperative and intraoperative confirmed existence is judged to be (+), when the digital technology can be worn for successful reconstruction is judged to be (+), either in the joint inspection tests to determine the (+), finally to the 3 ways to wear the positioning performance comparison.

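### The mimics and CTA + mimics arms differ in no described procedure, only in how a positive result is scored, and the CTA arm is not clearly separate either

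*Protocol article*

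**What the plan says.** Section 2.4 (Interventions) sets up three parallel arms: "Patients will be randomly divided into CTA group (n = 20), mimics group (n = 20) and CTA + mimics group (n = 20". It then gives one sentence to each arm:

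- CTA: "Patients in the CTA group will receive CTA examination of lower extremities".
- Mimics: "Patients in mimics group will receive digital technology in the positioning of perforator".
- CTA + mimics: "Patients in CTA + mimics group will receive CTA + digital technology".

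The same section goes on to describe surgery in all patients, and in that sentence has the surgeon identify the perforator by 3-D visualisation.

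Section 2.2 (Study method) describes a single workflow for the patients and assigns no step to an arm. Step 2 acquires the scan: "A 256-slice spiral CT (Philips, USA) will be used for continuous CTA scanning from bilateral anterior superior iliac spine to bilateral lower edge of patella". Step 3 tells staff to "obtain CTA data in DICOM format and import CTA data into 3-D15.0 software (Materialize, Belgium". Still within step 3, before segmentation begins, "The original CTA images will be scanned and observed in three orthogonal sectional views to determine the appropriate location of the perforation".

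Section 2.5 (Measurement of outcomes) plans a "Consistency analysis by CTA joint digital technology, digital technology and CTA" and gives a positivity rule for each method. CTA is positive when a perforator seen before surgery is confirmed at operation. The digital method is positive when the reconstruction succeeds. The joint method is positive when either component is positive.

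**The concern.** Section 2.4 treats digital reconstruction as something a patient can have with or without CTA. Section 2.2 makes CTA both the raw material of the reconstruction and its first reading step. If so, a patient in the mimics arm has already had what the CTA + mimics arm adds.

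What is at stake is the meaning of a randomised contrast. Flap survival depends on what is done to the patient. If two arms receive the same described care, a survival difference between them has no described cause. The localisation measures depend also on how a result is counted, so a difference could be produced by the counting rule and be reported as a benefit of adding CTA. The consistency analysis raises a related problem: agreement between methods has to be measured on the same patients, whereas parallel arms spread the methods over different patients.

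**Working it through.** The article gives no rates, effect size or power, so there is no calculation to reproduce beyond the arm sizes: 3 × 20 = 60, which agrees with the text. The check is mainly a comparison of sections.

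**1. Input to the digital method.** Section 2.2 names one source of thigh images for the software, the lower-limb CTA. The contrast CT in step 1 is for the lesion and the recipient area, not the thigh. As described, mimics without CTA cannot be carried out.

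**2. CTA reading inside the digital method.** Step 3 has the original CTA sections inspected to choose the perforator site before the model is built. So the digital workflow also contains a CTA read.

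**3. Procedures by arm.**

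| Described element | CTA | Mimics | CTA + mimics |
|---|---|---|---|
| Lower-limb CTA acquired | yes | yes (needed as input) | yes |
| CTA sections read for the perforator | yes | yes (step 3) | yes |
| Reconstruction built | not in its arm sentence; section 2.2 sets no limit by arm | yes | yes |
| 3-D positioning by the surgeon | apparently yes (section 2.4) | yes | yes |

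The last two columns are identical. They hold 20 + 20 = 40 of 60 patients. The first column is not clearly distinct from them.

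**4. Scoring by arm.** Mimics is positive if D (reconstruction succeeds). The combination is positive if D or C (CTA read positive). Every D-positive is also positive under the joint rule. In the same patients, therefore, joint sensitivity cannot be below digital sensitivity, and joint specificity cannot be above digital specificity.

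To show the size of this effect, assume that both component reads have the same sensitivity s. These values are not in the document.

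- If CTA reading rescues no digital miss, joint sensitivity = s.
- If the two reads miss independently, joint sensitivity = s + (1 − s) × s.

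| Assumed s | Full overlap | Independent reads |
|---|---|---|
| 0.70 | 0.70 | 0.70 + 0.30 × 0.70 = 0.91 |
| 0.80 | 0.80 | 0.80 + 0.20 × 0.80 = 0.96 |
| 0.90 | 0.90 | 0.90 + 0.10 × 0.90 = 0.99 |

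The scored difference under these assumptions runs from 0 to 0.21, 0.16 or 0.09, with no difference in care.

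**5. Readings available for agreement.** Under the either-positive rule, a combination patient must have a C and a D result, which together give the joint result. That guarantees paired readings in 20 patients. For the other 40, section 2.4 promises only one named method each. If instead the section 2.2 workflow is applied to all 60, every patient has a CTA series from which all readings can be taken, and parallel arms are not needed for the localisation question.

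**The case against.** The best defence is section 2.5. It separates the methods by scoring: a patient whose reconstruction fails but whose CTA read is positive counts as negative under mimics and positive under the combination. This stands. A reader might infer from section 2.2 that the mimics versus CTA + mimics contrast is empty, that its true difference is zero by construction, or that any significant result there must be a false positive. The documents do not support that for sensitivity, specificity and accuracy, where the rules allow the arms to differ.

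A second defence is that the arms may be meant to differ in which read guides the surgeon: the model alone, or the model plus a separate CTA read. That is a possible intention, but section 2.2 does not say so, and its step 3 puts a CTA read inside the digital workflow.

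A third concerns the consistency analysis. A reader might infer that parallel arms leave each patient with a single reading, so that agreement cannot be computed at all. That goes too far, because the 20 combination patients must have both component reads. The sentence in section 2.5 is also hard to parse and may mean agreement of each method with the operative finding, which parallel groups can supply. If it means agreement among the three methods, the pairing is guaranteed only in those 20.

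The brevity of a journal article does not explain the conflict. The workflow is set out in detail, and it is that detail which disagrees with the arm definitions.

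**Conclusion.** The point holds in this form and should be settled before the trial proceeds, because it concerns what is being randomised and no later analysis can repair it.

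- **Procedure and flap survival:** no described difference between mimics and CTA + mimics, which together hold 40 of 60 patients.
- **Sensitivity, specificity and accuracy:** a difference is possible, but it comes from the positivity rules. Higher sensitivity for the combination would not show that different care finds perforators better.
- **CTA arm:** not clearly separate, if the 3-D positioning in section 2.4 covers all patients, as it appears to. The problem may therefore reach beyond one of the three contrasts.
- **Consistency among the three methods:** paired readings are guaranteed in at most 20 patients.

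The conclusion rests on section 2.2 being the complete account of thigh imaging and applying to all arms. It does not depend on the assumed sensitivities, which only illustrate how far scoring alone could move the result.

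**What to change.** Reconcile sections 2.2, 2.4 and 2.5 so that each arm is defined by the images or reads that may be used to locate the perforator, and state whether the CTA arm has access to the 3-D model.

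**Localisation.** Read every patient's CTA series three ways: as plain CTA, as the reconstruction, and jointly. Record each reading before surgery and compare all three with the same operative finding. Compare methods with McNemar tests, or with generalised estimating equations if several perforators per patient are scored. Use kappa for agreement. When joint and digital readings are compared, report the either-positive rule alongside the result, since it fixes the direction of the sensitivity difference.

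**Flap survival.** Each patient has one flap, so this cannot be compared within patient and still needs separate arms. Make no mimics versus CTA + mimics claim for it. Merging those two arms (n = 40) against CTA (n = 20) is sound only if the CTA arm is first defined without the 3-D model.

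**Cost.** Changes to protocol and registry wording, and some extra desk reading of scans that section 2.2 already describes. No new patients or scans are needed. The three-arm headline comparison is lost.

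### Specificity, and any accuracy figure that needs true negatives, cannot be validly estimated: only positive calls are defined, and verification follows the imaging; sensitivity is likely biased upward unless confined to a fully explored field

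*Protocol article*

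**What the plan says.** The protocol article states its aim in section 2.1: "We aim to compare the efficacy including survival rate, sensitivity, specificity and accuracy" across the CTA, mimics and combined groups. Section 2.4 repeats these outcomes.

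Section 2.2 describes the imaging and the verification in sequence:

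- The scan covers both thighs: "continuous CTA scanning from bilateral anterior superior iliac spine to bilateral lower edge of patella".
- A perforator site judged suitable for the flap is picked from the images.
- Reconstruction is limited to one thigh: "the 3-D reconstruction area will be restricted to 1 side of the supply area with suitable cutting struts".
- A flap is designed on that model, transferred to the patient's skin and raised: "the flap will be surgically removed to verify the accuracy of perforator location".

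Section 2.5 gives the scoring rules:

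- For CTA, "when the CTA inspection found perforators preoperative and intraoperative confirmed existence is judged to be" positive.
- For the digital method, "when the digital technology can be worn for successful reconstruction is judged to be" positive.
- For the combination, a positive on "either in the joint inspection tests to determine the" joint positive.

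The article gives no rule for a negative call, no definition of a site verified to be free of perforators, and no unit of analysis (site, perforator, flap or patient).

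**The concern.** Sensitivity, specificity and overall accuracy come from a two-by-two table: the test's call, positive or negative, against a truth established independently of that call. Two things stand in the way here.

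First, where truth is established depends on the test. The flap is planned where imaging has shown a suitable perforator. Imaging-positive sites are opened by design, and imaging-negative sites are opened only if they happen to lie within the flap. This is partial verification.

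Second, the written scoring rules do not produce the table. The negative row is undefined. The CTA positive has the surgical finding built into it, while the digital positive does not, so the methods are not scored by the same rule.

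At stake is the main comparison of the trial. The specificity figures could not be interpreted, and the methods could be ranked by their scoring rule rather than by their performance. Real differences in sensitivity could also be compressed. No later analysis can recover negatives that were not recorded at surgery.

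**Working it through.** The article gives no expected sensitivity or specificity, so there is no figure to reproduce. The only design number used is 20 patients per group (section 2.4). Everything else below is an assumption, shown as a range.

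**1. Scoring rules side by side (section 2.5)**

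| Method | Positive if | Surgical finding part of the call? | Negative defined? |
|---|---|---|---|
| CTA | seen before surgery and confirmed at surgery | yes | no |
| Digital | reconstruction succeeds | no | no |
| Combined | either is positive | for the CTA part only | no |

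Specificity = TN/(TN + FP). For CTA, an unconfirmed finding cannot be positive, so FP = 0. Specificity is then TN/TN = 100% if any true negative is counted, and 0/0 if none is. Neither result says anything about CTA. The digital method has no such protection, so the two figures are not comparable.

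**2. Effect of partial verification on sensitivity**

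Let v be the share of imaging-negative sites verified divided by the share of imaging-positive sites verified. With true sensitivity Se,

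apparent Se = Se / (Se + (1 − Se)·v).

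| True Se | v = 1 | v = 0.5 | v = 0.25 | v = 0.1 | v = 0 |
|---|---|---|---|---|---|
| 0.70 | 0.700 | 0.824 | 0.903 | 0.959 | 1.000 |
| 0.80 | 0.800 | 0.889 | 0.941 | 0.976 | 1.000 |
| 0.90 | 0.900 | 0.947 | 0.973 | 0.989 | 1.000 |

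Example: Se = 0.80 and v = 0.25 give 0.80/(0.80 + 0.20 × 0.25) = 0.80/0.85 = 0.941. There is no bias at v = 1 and an upward bias for any v below 1. Differences between methods shrink as well: at v = 0.25, a true gap of 0.80 − 0.70 = 0.10 appears as 0.941 − 0.903 = 0.038.

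**3. Effect on specificity, if positive calls were scored before surgery**

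With true specificity Sp,

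apparent Sp = Sp·v / (Sp·v + (1 − Sp)).

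For Sp = 0.80 this is 0.800 at v = 1, 0.667 at v = 0.5, 0.500 at v = 0.25, 0.286 at v = 0.1 and 0 at v = 0. If v = 0 and no false positive is seen, the ratio is 0/0. Correcting the CTA rule alone would therefore not be enough.

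**4. Does analysis per patient avoid the problem?**

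Every patient has a flap raised (section 2.4), so verification is complete at that level, but true negatives are scarce. Let q be the share of patients without a perforator. The expected number per group is 20q, and the chance of none is (1 − q)^20.

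| q | Expected negatives per group | Chance of none |
|---|---|---|
| 0% | 0 | 1.00 |
| 2% | 0.4 | 0.67 |
| 5% | 1 | 0.36 |
| 10% | 2 | 0.12 |

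If both of two such patients were called correctly, the exact lower 95% limit for specificity would be 0.025^(1/2) = 0.16.

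**The case against.** A reader might infer that only the single chosen perforator is checked, that most missed perforators are never seen, and that sensitivity is therefore inflated. The document does not support that strength of claim.

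- Raising a flap exposes a territory, not a point. Some missed perforators and some false alarms within it can be seen. Section 2.5 also promises a record of the vascular anatomy and a comparison of preoperative with intraoperative findings, and nothing limits either to the target vessel. It does not, however, say that every perforator met is recorded.
- The share of missed perforators that goes unseen cannot be derived from the text.
- The bias in sensitivity is conditional. It disappears if the analysis is confined to a fully explored field, and the unit of analysis is not stated.
- The restriction to one side is given as a way to save segmentation work. It is not a verification rule and is only supporting evidence.
- Accuracy may mean accuracy of location, as it does in section 2.2. Raising the flap does check that.

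It can also be said that an operative record form and a unit of analysis belong in the full protocol, which is not shown. That is fair for the form itself. It does not answer the main point, because the article does state its outcomes, its verification step and its positive rules. Those statements do not fit together: a CTA positive that contains the surgical result cannot yield a meaningful specificity, whatever form is used.

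**Conclusion.** The point stands in a limited form. As written, specificity cannot be validly estimated or compared between methods, nor can any overall accuracy that needs true negatives. This follows from the text of section 2.5 and needs no numerical assumption: negatives are undefined, CTA false positives are zero by definition, and the digital method is scored by a different rule.

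For sensitivity the conclusion is weaker. An upward bias is likely unless the analysis is restricted to a predefined, fully explored field. Its size is unknown. For an assumed true sensitivity of 0.80 the apparent value lies between 0.80 and 1.00, and the 0.941 at v = 0.25 is one assumed point in that range, not an estimate for this trial. Perforator location accuracy and flap survival are not affected by this point.

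**What to change.** 1. Score each method's preoperative call separately from the surgical finding, by the same rule for CTA, digital and combined, and fix the call before surgery.
2. Limit the accuracy analysis to the field that is dissected anyway, name the unit of analysis, and record every perforator met in that field, whether predicted or not.
3. Report the detection rate (predicted and found / all found in the field), the positive predictive value (confirmed / predicted) and the distance between predicted and actual exit points.
4. Drop specificity and overall accuracy. Alternatively, keep them for fixed cells marked over the planned flap before surgery: call each cell present or absent on imaging, and score the same cells at dissection.
5. State that the results apply to the dissected field on the selected side.

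The cost is revised outcome wording and a short operative record, with no wider dissection. The downside is that the specificity headline is lost, or narrowed to the marked cells.
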